#### Demographic and socioeconomic indicators of households

Information on socio-economic status, gender, ethnicity, level of education, marital status, and occupation of the household head, water, sanitation, hygiene (WASH) and food insecurity will be collected. Household information will be captured from the head of the household or any knowledgeable member of the household (aged 18 years or more).

#### Dietary intake

Dietary intake will be assessed using the USAID FANTA Household Dietary Diversity Scale (HDDS) and a 24-hour dietary recall questionnaire. The 24-hour recall will be conducted for the entire sample at baseline, midline, and endline, covering weekdays and weekends to capture dietary variability. Detailed food information will include description, additives, combinations, brand (if relevant), quantity, time, occasion, source, and consumption location (home or elsewhere). Interviewers and staff will be familiar with local foods, aided by guidance documents. Local utensils and portion-size photographs will assist in estimation.

#### Morbidity

Incidence and duration of diarrheal episodes and respiratory tract infections will be recorded every two weeks throughout the study.

#### Anthropometric measurements

Trained research staff will conduct anthropometric assessments at households and schools. Weight and height measurements will be recorded to the nearest 0.1 kilograms and centimeters, respectively. This will be done with participants in light clothing and without shoes, using a Seca digital floor scale (model 813) and Seca stadiometer (model 213). Mid-Upper Arm Circumference (MUAC) and waist circumference will be determined using standardized procedures and a MUAC measuring tape (Seca 201). All measurements will be taken in duplicate by two research staff members, and if discrepancies exceed 1 cm for height, 0.5 kg for weight, or 0.5 cm for MUAC/waist circumference, a third measure will be taken by the team leader and recorded using standardized procedures.

#### Biochemical sample collection

A certified phlebotomist will supervise blood collection. 23-mm gauge needles will be used for adolescents and women of reproductive age, with trace element-free tubes for blood collection. Used needles, sharps, and other consumables will be disposed-off safely. Strict personal hygiene will be maintained, including the use of disposable gloves and hand sanitizer. Skin cleaning and vein visibility will be ensured, and 5 ml of venous blood will be collected. Samples will be labelled with barcoded stickers. After labeling, the collection tubes will be left undisturbed for 30 minutes, and then centrifuged at 3000 rpm for 10 minutes. Serum (at least 1.0 ml) will be transferred to pre-labelled tubes and then placed in zip-lock bags. These serum samples will be stored in cool boxes at 2 to 8°C with the inclusion of ice packs. Used consumables will be safely disposed of.

### Data analysis

#### Biochemical variables

Analysis of samples will be conducted at Nutrition research lab, Aga Khan University, where external quality assurance (VITAL-EQA) is managed by Centers for Disease Control and Prevention (CDC). Individual biomarker concentrations will be used to determine deficiency using standard cut-offs for age and sex. CRP concentrations will be used to identify inflammation for all participants. We will check whether adjustment is necessary for serum zinc concentration and will be adjusted according to the BRINDA project guidelines to determine zinc deficiency (VAD) and if so present both adjusted and unadjusted values. Fasting blood glucose and blood Hb1C levels will be measured using latex agglutination inhibition and photometric assays, respectively on cobas c 311 biochemistry analyzer (Roche Diagnostics). Serum zinc levels will be measured using flame atomic absorption spectroscopy on Thermo Fisher iCE 3300 AAS Atomic Absorption Spectrometer.

#### Food testing

Zinc is quantified in wheat seeds using Flame Atomic Absorption Spectrometry. Reagents include a zinc master standard (1000 mg/L), de-ionized water, nitric acid, hydrochloric acid, plasma zinc controls, and wheat flour SRM NIST 1567B. The sample preparation involves grinding the seeds into a fine powder, wet digestion with an acid mixture, and filtration. The assay calibration is performed using a linear graph method with working standards (0.03 ppm to 0.50 ppm) and a blank solution. For zinc analysis, an (air/acetylene) flame at a flow rate of 1.0 L/min, providing a temperature of 2500°C, is utilized for the atomization of gaseous zinc molecules. The zinc analysis further involves the detection wavelength of 213.9 nm, utilizing an automatic monochromator calibration with both the deuterium lamp and the zinc hollow cathode lamp. The analysis of filtered wheat seed samples is performed without further dilution, with each sample run in triplicates. Blank solutions are prepared, and standard deviation calculations ensure data reliability. Plasma controls and NIST wheat flour SRM (1567B) are included in each batch to ensure accuracy.

The quantification of phytate content in wheat seeds holds significance for gaining insights into nutritional profiles and refining food processing techniques. To accomplish this, the Megazyme Kit (K-PHYT 05/19) was utilized, providing a methodical framework that incorporates essential reagents like buffers, phytase and alkaline phosphatase suspensions, and phosphorus standards. The preparation of the phosphorus calibration curve involves creating standard phosphorus solutions with specified volumes and DI water. The subsequent calculation process determines the absorbance (A655) for each standard, leading to the derivation of ΔA phosphorus and mean M, which is then used to calculate the phosphorus content of test samples. Sample extraction is started by adding 0.5g of the ground wheat sample into a beaker and then10.0mL of 0.66M HCl is pipetted into the beaker. This mixture is then stirred vigorously using an electronic magnetic bead stirrer for at least 3 hours at room temperature. After stirring the mixture for a minimum of 3 hours, the clear extract obtained by centrifugation at 13000 RPM for 10 minutes is neutralized using 0.75M NaOH (1:1) for the enzymatic dephosphorylation reaction. The colorimetric determination of phosphorus involves pipetting 1.00 mL of the sample, control, or phosphorus standard, adding 0.50 mL of the color reagent, and incubating in a water bath at 40°C for 1 hour. The absorbance at 655 nm (A655) is then read within 3 hours. For phosphorus/phytic acid determination, absorbance values for "Free Phosphorus" and "Total Phosphorus" samples are obtained, and their concentration is calculated using a formula considering mean M, dilution factor, absorbance change, and relevant factors. The entire process ensures accurate and reliable results for phosphorus and phytic acid analysis in wheat seeds.

#### Anthropometric variables

Anthropometric variables including the average height (m), weight (kg), waist circumference and MUAC would be collected in duplicate and the average (mean) of acceptable paired measures will be used in the analysis. Participant Body Mass Index (BMI) will be calculated and converted to BMI-for-age z-scores (BAZ) along with height-for-age z-scores (HAZ) according to chronological age using the WHO Growth Reference for Adolescents and WHO-package for R. Participants with a HAZ <-2 SD will be classified as stunted; severe thinness with a BAZ ≤ -3 SD; thinness with a BAZ > -3 SD to ≤-2 SD, normal weight with a BAZ >-2 SD to <+1SD, overweight with a BAZ >+1 SD to < +2 SD and, obese with a BAZ ≥+2 SD. The prevalence of anthropometric indicator categories will be reported as the proportion of participants who did not achieve the respective cut-off. MUAC will be assessed using cut-offs outlined in the Integrated Management of Adolescent and Adult Illness (WHO) as the proportion of participants with MUAC < 160 mm.

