#### Secondary

Body Mass Index (BMI)—Severe thinness, thinness, normal weight, overweight, obeseRed blood cell membrane fatty acids concentrationsAnemiaBlood PressureSchool attendanceMorbidity–Diarrhea, Acute respiratory infection (ARI) etc.

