### Eligibility criteria

The study will include adolescents (aged 10–19 both male and female) and adult women (aged 20–40). Participants would be eligible if they can consume wheat flour (no celiac disease), are not severely malnourished, pregnant, or lactating at enrollment, with no known chronic disease, and not enrolled in any other nutrition program or taking micronutrient supplements. Individuals planning to leave the study site during the study period will also not be eligible. The enrollment has started in Aug 2023.

For the adult women, an additional eligibility criterion will be to assess their risk for T2DM. These risk factors were modified from an existing risk assessment scale, FINDRISC (Finnish Diabetes Risk Score) and Type 2 Diabetes Risk Test by American Diabetes Association (ADA) [25, 26]. Adult women with any one of the following risk factors will be eligible to be enrolled in the study.

BMI (>25kg/m^2^)Waist circumference (> 31 inches)Family history of diabetesHbA1c (>5.1%)FBG (>100mg/dl)Homeostatic Model Assessment of Insulin Resistance (HOMA-IR) (>2)

The HbA1c threshold for prediabetes are lower in Pakistan population compared with international guidelines, hence we have kept this as 5.1% [27].

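### BMI is listed as a secondary outcome by category and MUAC is summarised by a cut-off; no continuous anthropometric endpoint is named, so power is lost if the categories are what is tested

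*Protocol article*

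**What the plan says.** Under Outcomes, Secondary, the protocol article gives the BMI outcome as "Body Mass Index (BMI)—Severe thinness, thinness, normal weight, overweight", with obese as the fifth class. The Anthropometric variables section defines the classes by BAZ, for example "severe thinness with a BAZ ≤ -3 SD" and "thinness with a BAZ > -3 SD to ≤-2 SD". It then states: "The prevalence of anthropometric indicator categories will be reported as the proportion of participants who did not achieve the respective cut-off". MUAC is to be assessed "as the proportion of participants with MUAC < 160 mm"; MUAC does not appear in the Secondary list.

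The same section also describes continuous quantities. For duplicate readings, "the average (mean) of acceptable paired measures will be used in the analysis", and BMI is "converted to BMI-for-age z-scores (BAZ) along with height-for-age z-scores (HAZ". The section on baseline, midline and endline data collection has weight, height and MUAC measured at both baseline and endline.

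Under Eligibility criteria, participants must be people who "are not severely malnourished, pregnant, or lactating at enrollment"; no BAZ, BMI or MUAC threshold defines severe malnutrition. Trial analysis sends categorical variables to chi-square and continuous outcomes to one-way ANOVA. It adds linear or logistic mixed models with a time-by-group interaction and does not say which variable goes to which model.

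**The concern.** The Introduction includes anthropometric outcomes in the trial's aim. The only anthropometric summaries written down are class prevalences and one MUAC proportion. A proportion registers a change only when a participant crosses a line, so a modest shift of the whole distribution is largely invisible to it.

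Eligibility may add to this. If the undefined exclusion of severely malnourished people corresponds to BAZ ≤ −3, the severe-thinness class starts empty and can fill only through deterioration over six months.

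Two things are at stake. One is power on a secondary outcome. The other is that the tested form of the outcome stays open, so it could be chosen after the data are seen.

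**Working it through.** **Plan's own figure.** The protocol states no sample size or power for anthropometry. Its 250 per arm rests on serum zinc and HbA1c. If 0.12 is read as a 12% relative difference in zinc, 0.12 × 79.5 = 9.54 μg/dL and n = 2 × (1.96 + 0.84)² × 35.9² / 9.54² ≈ 223. Then 223 / 0.9 ≈ 248, close to 250. This says nothing about BAZ.

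**Inputs from the protocol.** There are 210 adolescents per arm and 10% dropout: 210 × 0.9 = 189. Alpha is 0.05, taken as two-sided. The severe-thinness cut-off is BAZ ≤ −3, and thinness runs from above −3 to −2.

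**Assumptions not in the protocol.** BAZ SD is 1.0–1.1, mean BAZ −0.5 to −1.5 and baseline–endline correlation r 0.8–0.9. Entry is restricted to BAZ > −3, and the true shift is 0.15 or 0.25 BAZ. Comparisons are between two arms, with no multiplicity adjustment.

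**Mean BAZ adjusted for baseline.** SE = SD × √(1 − r²) × √(2/189); power = Φ(shift/SE − 1.96).
- SD 1.1, r 0.8: SE = 1.1 × 0.6 × 0.1029 = 0.0679. Shift 0.15: Φ(2.21 − 1.96) = 60%. Shift 0.25: Φ(3.68 − 1.96) = 96%.
- SD 1.0, r 0.9: SE = 0.436 × 0.1029 = 0.0448. Shift 0.15: Φ(3.35 − 1.96) = 92%. Shift 0.25: nearly 100%.

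Simulation over the same grid gives about 56–93% and 95–100%.

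**Proportion with BAZ ≤ −2.** Endline BAZ given baseline b is normal with mean μ + r(b − μ) + shift and SD × √(1 − r²), averaged over b > −3. SE = √{[p₁(1 − p₁) + p₂(1 − p₂)]/189}.
- Mean −1, SD 1, r 0.9, shift 0.15: p₁ = 0.139, p₂ = 0.105, SE = 0.0337, power = Φ(0.034/0.0337 − 1.96) = 17%.
- Same case, shift 0.25: p₂ = 0.086, power about 38%.

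Simulation over the grid gives about 12–25% at 0.15 and 21–54% at 0.25; the closed form agrees within about a point. At shift 0.15 and SD 1.1, logistic regression adjusted for baseline thinness reaches only 11–32%.

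**Where the gap comes from.** At mean −1 and shift 0.25 (SD 1, r 0.90–0.95), power is 38% on the proportion and 72–73% on mean BAZ without baseline adjustment. With adjustment it is 95–100%. Dichotomising and leaving out the baseline value both contribute.

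**Cell sizes without a shift.**
- Severe thinness: for mean −1, SD 1, r 0.9, 0.0095 × 189 = 1.8 per arm. Over the grid it is about 0.6 to 8.
- Thinness (−3 to −2): in the same case 0.130 × 189 = 24.5 per arm. Across scenarios with SD 1 and r 0.90–0.95 it is about 11 to 46, so this class is populated.

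**MUAC.** The protocol gives no mean or SD, so neither power nor the expected count below 160 mm can be computed.

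**The case against.** The strongest reply is that nothing restricts anthropometry to categories. Averaged measurements go into the analysis, BAZ and height-for-age z-scores are computed, the abstract speaks of anthropometric measurements, and Trial analysis provides ANOVA and linear mixed models for secondary data too. On this view the prevalence sentence only describes presentation, and the choice of metric belongs in an analysis plan that is not shown. This stands to the extent that a reader might infer that BMI is defined only by categories and the continuous data are discarded; the text does not support that.

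It does not settle the matter. The averaging sentence says how duplicates are combined, and the linear methods are generic. Neither names a continuous anthropometric endpoint, whereas the article itself writes the BMI outcome down by class.

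Other points stand. The sparse severe class is an inference, because severe malnutrition has no stated threshold, and no separate test of that class is planned. MUAC is not a listed outcome. Classes at both ends matter in a trial of undernutrition and metabolic risk, and a higher mean BMI is not clearly a benefit for everyone. That supports keeping the class tables and a two-sided test; it does not support testing only the classes.

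**Conclusion.** The concern holds in a limited form. The BMI outcome is listed by category, MUAC is summarised by one cut-off, and no continuous anthropometric endpoint is named. If the categories are tested, power on BAZ ≤ −2 is about 12–25% at a 0.15 shift and 21–54% at 0.25, against 56–93% and 95–100% for baseline-adjusted mean BAZ. The BAZ mean, SD, correlation, entry threshold and shift are all assumptions, but the adjusted mean had the higher power in every scenario examined.

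A reader might go further and conclude that a real effect is almost certain to be reported as none. The protocol does not support that: it would require the categories to be the only analysis and the shift to be small. Only the severe-thinness class is likely to be sparse, and only if the exclusion corresponds to BAZ ≤ −3. These are secondary outcomes, so the primary conclusions are not affected.

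**What to change.** Name the tested anthropometric outcomes as endline mean BAZ in adolescents, mean BMI in adult women and mean MUAC. Adjust each for its own baseline value and the randomisation strata (gender and age group). Add MUAC to the Secondary list, since it is not there now. Keep the five BMI classes and MUAC < 160 mm as descriptive tables by arm. State the threshold used for the severe-malnutrition exclusion, so that readers can tell which classes were closed at entry.

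The cost is a change of wording before unblinding, with no new data. The small downside is that class prevalences, which programme readers find useful, are no longer formally tested.

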#### Food security and 24-hour dietary recall

Using the eight dichotomous questions (yes/no) within the Household FIES, households will be classified based on the total number of affirmative responses ranging from 0–8. As recommended by FAO, Rasch modelling techniques will be used.

The data collected from 24-hour recall will reveal the nutrient consumption patterns of each child beyond the study-provided food, aiding in assessing the actual intervention impact. Given the lack of a food composition database for Pakistan, we intend on using a database compiled by a recent study in Pakistan (MAL-ED) which compiled nutrient data from various sources. This comprehensive database includes foods from multiple references, including World Food Dietary Assessment System, USDA National Nutrient Database, NUTTAB online database, Composition of Foods Integrated Database, and the Food Composition Table for Bangladesh. If values could not be located through these sources, values were calculated using common recipes by either the PKN or INV sites of the MAL-ED study [34–44]. The final contents of the MAL-ED Pakistan Food Composition Table consist of a combination of individual food items pulled from the sources referenced above, and nutrient values derived from calculating nutrients in the recipes collected as part of the study.

A trained nutritionist will assign food codes, and retention factors will be applied to account for nutrient changes due to different cooking methods. The mean total intake of each nutrient will be calculated using frequency weight and nutrient content for each food.

### Trial analysis

This trial will adhere to CONSORT guidelines for randomized trials, with primary analysis on an intention-to-treat basis [22]. Both primary and secondary data will be analyzed following the same principle. Descriptive statistics will include mean and standard deviation for symmetrically distributed continuous variables, median and interquartile range for asymmetrically distributed ones, and frequency with percentages for categorical data. Associations between dependent and independent categorical variables will be accessed using chi-square test, while one-ANOVA will be used to assess difference in continuous outcomes by intervention groups. Significant association further assessed by post-hoc test adjusting for multiple comparisons. Multivariate analysis will be performed using mixed effect linear or logistic regression to assess the impact of intervention over time by including time and group interaction. The time and intervention group will be treated as fixed effect while students included in the model as random intercept. The potential confounding factors that are imbalance at baseline will also be included as fixed effect in the model. The minimal adequate model for regression will be computed using the backward procedure. Statistical Significance will be set at p-value of <0.05. To assess the robustness of the findings, a sensitivity analysis will be conducted, and a dose-response relation will also be assessed.

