### Data collection

Baseline and endline measurements will be conducted for all participants, whereas for midpoint assessments, sampling scheme will be assessed by randomized, arm-based stratified selection so that a third from each arm is tested at two additional time points.

For all study visits, electronic app-based questionnaires will be used to guide personnel in conducting structured interviews with the study participants at baseline and endline. Data on 24-hr dietary recall will be collected in paper-based questionnaires. A summary of all monitoring and visit-specific forms will be used throughout the study.

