### Baseline, midline, and endline data collection

Participants will undergo assessments at baseline and endline, where we will gather data on socio-demographic factors, dietary intake via 24-hour dietary recall, anthropometric measurements (weight, height, MUAC, waist circumference), blood pressure measurements, and blood samples will be collected for biochemical analysis, including serum zinc levels, FBS, HbA1C, and insulin at both time points. Lipid profile and RBC membrane fatty acids will be assessed only at the endline. At midline, we will conduct 24-hour dietary recalls, measure serum zinc and HbA1C for a subset from each group. The data for morbidity (diarrhea and ARI) will be collected fortnightly for the entire duration of the intervention.

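### The primary outcome HOMA-IR is given only as a cut-off (>2), which reads as yes/no; if analysed only that way, a large, avoidable part of its information is lost

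*Protocol article*

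**What the plan says.** The primary outcome list in the protocol article (Outcomes, Primary) contains serum zinc concentration, zinc deficiency, HbA1c, HOMA-IR and the lipid profile. HOMA-IR is the only entry with a numeric threshold attached, a referenced cut-off of more than 2, and no separate entry gives it as a value.

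The Trial analysis section sets rules by type of variable and assigns no outcome to either type. For categorical variables: "Associations between dependent and independent categorical variables will be accessed using chi-square test". The same sentence goes on to say that "one-ANOVA will be used to assess difference in continuous outcomes by intervention groups". For change over time: "Multivariate analysis will be performed using mixed effect linear or logistic regression".

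The components of HOMA-IR are measured in everyone. The Data collection section says "Baseline and endline measurements will be conducted for all participants", and the section on baseline, midline and endline data collection lists blood tests "including serum zinc levels, FBS, HbA1C, and insulin at both time points".

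The same threshold appears among the alternative entry criteria for adult women: "Homeostatic Model Assessment of Insulin Resistance (HOMA-IR) (>2".

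**The concern.** An outcome defined by whether a value exceeds 2 is binary. Under the generic rules it would go to the chi-square test and to the logistic form of the mixed model. Such an analysis records only which side of the line each participant is on. A participant whose HOMA-IR falls from 4 to 2.5, or from 1.8 to 1.2, counts as unchanged.

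This matters because HOMA-IR is one of the trial's primary metabolic outcomes. In each group of 250, 210 are adolescents, and the metabolic risk criterion for entry applies only to adult women. The share of participants above 2 could therefore be well below one half, and the loss from a split grows as that share moves away from one half. A real but moderate shift could be reported as no effect although the stored glucose and insulin values would show it.

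**Working it through.** **The plan's own figure.** The protocol gives no SD, prevalence or power for HOMA-IR. Its sample size rests on serum zinc and HbA1c. Reading the 0.12 effect size for zinc as a 12% difference in the mean:

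- difference = 0.12 × 79.5 = 9.54 μg/dL, SD 35.9;
- n per group = 2 × (1.960 + 0.842)² × (35.9 / 9.54)² ≈ 222.4, rounded up to 223;
- with 10% dropout, 223 / 0.9 = 247.8, so 248, close to the stated 250.

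HOMA-IR plays no part in this, so nothing below changes the 250 per group.

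**Inputs for HOMA-IR**

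- From the document: 250 per group and 10% dropout, hence 225 evaluable per arm; alpha 0.05; power 0.80.
- Assumed: two-sided testing; log HOMA-IR roughly normal; arms differ by a shift; the proportion p above 2 in the comparison arm, shown from 50% to 10%.

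**Information kept by a split.** The efficiency of the binary comparison relative to the continuous one is φ(z)² / [p(1 − p)], where z is the normal quantile at 1 − p and φ is the normal density.

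- At p = 0.5: z = 0, φ = 0.3989, efficiency = 0.1592 / 0.25 = 0.637.
- At p = 0.1: z = 1.2816, φ = 0.1755, efficiency = 0.0308 / 0.09 = 0.342.

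**Power.** The shift with 80% pairwise power on the continuous scale is (1.960 + 0.842) × √(2/225) = 0.264 SD. For a fall in HOMA-IR of that size, the proportion above 2 drops from p to q = 1 − Φ(z + 0.264). Power for the two proportions is Φ(|p − q| / √{[p(1 − p) + q(1 − q)] / 225} − 1.960). At p = 0.5 this is Φ(0.1042 / 0.04663 − 1.960) = Φ(0.274) = 0.61.

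| p above 2 | Efficiency | Information lost | Effective n of 225 | q after shift | Power as >2 |
|---|---|---|---|---|---|
| 50% | 0.637 | 36% | 143 | 39.6% | 61% |
| 30% | 0.576 | 42% | 130 | 21.5% | 54% |
| 20% | 0.490 | 51% | 110 | 13.4% | 46% |
| 10% | 0.342 | 66% | 77 | 6.1% | 33% |

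A pooled variance under the null gives 60% in the first row and the same rounded values in the others. A shift upward would have 41% power at p = 10%. The loss is symmetric in p, so 90% above 2 also loses 66%. At p = 5% it is 78%, so the range shown is not an upper limit.

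**The case against.** The strongest reply is that the protocol never says HOMA-IR will be analysed as yes/no. The Trial analysis section does not name it, the sentence with the chi-square test also provides ANOVA for continuous outcomes, and the mixed model may be linear or logistic. The cut-off in a terse list could be a clinical reference value reported beside the continuous measure, and a condensed article may leave scale and transformation to an analysis plan that is not shown. This stands in part: a binary analysis is inferred and the size of the loss is conditional.

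The reply does not remove the point. The list gives serum zinc in both forms, so its authors write out both where they want both. HbA1c has an entry threshold of 5.1% in this protocol yet is listed without it. BMI, a secondary outcome, is listed with categories, and the section on anthropometric variables does compute BMI and z-scores first; but it then reports those categories as proportions, which favours the categorical reading. What defines a primary outcome belongs in the protocol itself.

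Three stronger inferences are not supported:

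- A reader might say that a single cut-off conflicts with the use of "standard cut-offs for age and sex" in the section on biochemical variables. That sentence concerns deficiency, and HOMA-IR is not a deficiency marker.
- A reader might say that using the same threshold for entry biases the result, because women admitted above 2 can drift back below it. The threshold is one of six alternative routes, open only to the 40 adult women per group, and regression to the mean is expected equally in every randomised arm. It adds noise in some women and does not bias the comparison.
- A reader might conclude that the trial is underpowered as a whole. The sample size was set on other outcomes and does not change.

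**Conclusion.** The point holds as a badly fixed definition of a primary outcome. Read as written, HOMA-IR is binary, and the analysis section leaves open which of its two sets of methods applies. A reader might infer that the protocol commits to a chi-square test on HOMA-IR and discards a known share of its information. The text supports neither: no test is assigned to HOMA-IR, and the loss depends on a prevalence that the document does not state.

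Conditional on analysis only as above or below 2, on approximate normality of log HOMA-IR and on a shift between arms, the loss runs from 36% at 50% prevalence to 66% at 10%. Even the most favourable prevalence costs more than a third of the information. If a continuous analysis was intended all along, the outcome list misdescribes it and needs the same correction.

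**What to change.** In the primary outcome list, replace the cut-off entry with continuous HOMA-IR at endline, on the log scale, calculated from the fasting glucose and insulin already scheduled for all participants. In the Trial analysis section, state that it is analysed with the linear model, adjusted for baseline log HOMA-IR, and reported as a ratio of geometric means between arms. Keep the proportion above 2 as a supporting summary.

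This needs no new data, visits or participants. The small downside is that the headline result becomes a ratio of geometric means, which is less immediate than a proportion above a threshold; the proportion remains in the report. The change should be made and dated before the colour code is broken.
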